### 2.1. Variables

#### 2.1.1. Independent Variable: School-Based Sexual and Reproductive Health Services

(a)Availability of services(b)Accessibility of services(c)Perceptions towards services and providers

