#### 2.4.2. Considerations

*π*T = Proportion of pregnant girls in group 1 approximately 29% (0.29). This is the current pregnancy prevalence in Bunyoro region (29%).

*π*C = Proportion of pregnant girls in group 2 approximately 19% (0.19). This is the expected reduction in prevalence of adolescent pregnancy after the intervention.
$$\begin{array}{lll} \mathrm{Effect}\mathrm{size} & = & 10\%[\delta \mathrm{Binary}=(\pi T-\pi C)],\mathrm{which}\mathrm{is}0.1\\ \alpha & = & 0.05(\mathrm{two}-\mathrm{sided})\\ \beta & = & 0.2\\ Z\alpha /{}_{2} & = & \mathrm{Desired}\mathrm{significance}\mathrm{level}\mathrm{at}5\%(1.96)\\ Z_{1-\beta } & = & \mathrm{Desired}\mathrm{power}\mathrm{at}80\%(0.842)\\ \mathrm{Type}\mathrm{of}\mathrm{test} & = & \mathrm{Two}-\mathrm{sided} \end{array}$$

Absolute risk reduction = 10%;

**Step One:** Formula for determining the number of subjects per group *^n^*_Individual_Binary_ for a two-sided significance level *α* and power 1 − *β*:$$\begin{array}{c} =\frac{{\left(1.96+0.842\right)}^{2}[0.29(1-0.29)+0.19(1-0.19)]}{{\left(0.29-0.19\right)}^{2}}\\ =(2.802)2[0.2059+0.1539]\\ =(7.851\times 0.3598)/0.01\\ =282.5\\ \sim 283\mathrm{individuals} \end{array}$$

**Step Two:** In order to adjust for the clustering effect, the sample size (*^n^*_Individual_Binary_) was inflated by a Design Effect (DE) to get an adjusted sample size (*^n^*_Cluster_Binary)_ [31]. Therefore, to determine the adjusted sample size per study group (*^n^*Cluster_Binary) for a Cluster Randomized Controlled Trial (cRCT), with a binary outcome, we multiply it with the Design Effect (DE):*^n^*_Cluster_Binary_ = *^n^*_Individual_Binary_ × Design effect
*^n^*_Cluster_Binary_ = *^n^*_Individual_Binary_ × [1 + (*m* − 1) *ρ*]
where *m* is the fixed cluster size and *ρ* is the Intra-cluster correlation coefficient (ICC). ICC is the ratio of the between-cluster variance to the total variance of an outcome variance and quantifies the correlation between the outcomes of any two individuals within the same cluster [31]. Since there is no previously published data/study in Uganda documenting the ICC, an ICC of 0.01 was considered because it is within the recommended inter-quantile range ICC (0.011–0.094) for previously undocumented ICC. Campbell and Walters [24] recommended a minimum cluster size of 50 subjects per cluster to cater for secondary outcomes; therefore, a fixed cluster size of 60 individuals was considered for this study.

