## 3. Analysis

Analysis will be done using aggregate cluster-level analysis; regression analysis using individual patient data with robust standard errors; random-effects (Res) models using individual patient data; and population averaged models using individual patient data with regression coefficients estimated using generalized estimating equations (GEEs). In this study, data exploration will be done to visualize the general feature of the data then the key analysis will be by SPSS version 20 at both cluster and individual levels. Both descriptive and inferential statistics will be analyzed allowing for the association between SBSRH service and prevention of adolescent pregnancy (occurrence of pregnancy, sexual behavioral change). The intent to treat analysis will be used to analyze patients according to their random treatment assignment, which is the intended treatment, not the treatment actually received.

Descriptive summary statistics of the clusters and individuals such as frequencies, mean, medians and standard deviations will be used to describe the characteristics of the study population on sex, age, socio-economic, education level, pregnancy status and sexual behavior, among others. Summary statistics for categorical data will be displayed in form of mean, proportion, frequencies and percentages depending on the nature of the data.

To determine the association between the dependent and independent variables, a general logistic regression model will be employed and two steps will be followed. First, each variable will be entered into a binary logistic regression model. Second, variables that are found to be significant at a p-value of 0.05 will be fitted into a multiple logistic regression model to identify independent factors of influencing occurrence of adolescent pregnancy. Variables that remain significant at a p-value of 0.05 will be further analyzed using multivariate logistic regression model and variables will be identified as independent factors influencing incidence of pregnancy and behavioral change.

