Based on the above logistical regressions, inferential statistics such as t-test and chi square test will be used to determine the similarity in the two groups using their baseline data (baseline comparison) and to determine relationships as well as associations between variables. Chi square tests will be used to test the relationships between categorical variables, while independent t-tests will be carried out to determine differences between the study groups for continuous variables with normal distribution.

Cluster level: The summary measure for each cluster (mean or proportion) will be calculated, because each cluster provides only one data point and the data will be considered to be independent while allowing standard statistical tests to be used. Multiple regressions will be used for the data summarized at the cluster level.

Individual level: During the two stage data analysis process, individual level covariates will be incorporated into the cluster analysis while accounting for the intra-cluster correlation, thus increasing the statistical power of the analysis. Statistical tests will be conducted taking into account for the clustering effect.

Qualitative data collected during the key informant interviews and focus group discussions will be transcribed and typed into a Microsoft Word computer program. These notes will be transcribed verbatim to ensure complete capturing of the responses of the study participants. Thematic analysis will be used to analyze qualitative data from key informant interviews and focus group discussions using the Atlas qualitative data analysis software version 7 (atlasti.com). Themes and sub-themes relevant to the objectives of the study will then be identified to enable development of qualitative coding and code definitions. Codes will be grouped into categories and then themes. The coded transcripts will be analyzed by running query reports and primary documents tables of codes by objective or theme and results will be used to explore the magnitude of the issues from the various focus group discussions and key informant interviews. Quotes illustrating meaning or key messages from the analysis will be selected based on the code count or how illustrative to the theme the quotes will be.

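### No single analysis decides the pregnancy question, and the stated p<0.05 screening, with no cluster term, can remove the randomised arm from the model

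*Protocol article*

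**What the plan says.** All of the analysis text is in section 3 of the protocol article.

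- It opens with a list: "Analysis will be done using aggregate cluster-level analysis; regression analysis using individual patient data with robust standard errors", then random-effects models and GEE. The main analysis is to be run in SPSS at both cluster and individual levels. None of these is called primary.
- Intention-to-treat by randomised assignment is stated.
- A general logistic regression is then assigned to the association between the dependent and independent variables. Each variable is entered singly, and "variables that are found to be significant at a p-value of 0.05 will be fitted into a multiple logistic regression model". Those still significant at 0.05 go into a further model. No cluster term appears in this paragraph, and the arm is not exempted from the screen.
- Section 2.1.1 names the school-based services as the independent variable and breaks it down as "a)Availability of services(b)Accessibility of services(c)Perceptions towards services and providers".
- Chi-square tests are planned for categorical variables, and "independent t-tests will be carried out to determine differences between the study groups", limited to continuous, normally distributed variables.
- The cluster-level paragraph plans one summary per school. The individual-level paragraph ends: "Statistical tests will be conducted taking into account for the clustering effect".
- Structural equation modelling is given the task of establishing the statistical significance of the service model in preventing pregnancy.

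**The concern.** Three things are left open that the text should settle.

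1. **Which result decides.** Several analyses can answer the same question, and the article does not say which p-value counts.
2. **Whether the arm stays in.** The service package is the independent variable and the screen covers each variable. Read literally, the randomised comparison must earn its place at p<0.05. A comparison that fails drops out instead of being reported with its interval, and one reported only because it passed is biased away from the null.
3. **Whether clustering is respected.** The logistic and chi-square paragraphs describe standard tests with no cluster adjustment, while a later sentence says tests will allow for it. An analyst could follow either.

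The trial is meant to inform policy, so both a spurious positive and a missing estimate would matter.

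**Working it through.** **Inputs from the article (sections 2.4 and 2.5).** Rates 0.29 and 0.19; two-sided alpha 0.05; power 80%; ICC 0.01, with a cited range of 0.011 to 0.094; 60 girls per school; 9 schools per arm; 10% non-response.

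**The article's own sample size, reproduced.** (1.96 + 0.842)² × [0.29×0.71 + 0.19×0.81] / 0.10² = 282.5 per group. Design effect DE = 1 + 59×0.01 = 1.59. 282.5 × 1.59 = 449 per group, 898 in total; × 1.10 = 988; / 60 = 16.5, raised to 18 schools, or 1080 girls. The sample size therefore allows for clustering. The question is whether the tests do.

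**Type I error if girls are treated as independent.** The naive statistic has variance DE instead of 1, so the error is 2[1 − Φ(1.96/√DE)]. At ICC 0.01: √1.59 = 1.261, 1.96/1.261 = 1.554, error 0.120. This was checked by beta-binomial simulation (40,000 null trials, 9 v 9 schools of 60, rate 0.29 in both arms):

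| ICC | DE | Formula | Simulated, unadjusted logistic Wald | Simulated, school-level t-test |
|---|---|---|---|---|
| 0.01 | 1.59 | 0.120 | 0.122 | 0.052 |
| 0.011 | 1.649 | 0.127 | 0.126 | 0.051 |
| 0.05 | 3.95 | 0.324 | 0.319 | 0.047 |
| 0.094 | 6.546 | 0.444 | 0.445 | 0.050 |

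The unadjusted chi-square agrees with the Wald test (0.123 at ICC 0.01). With 54 girls analysed per school (60 less 10%), DE at ICC 0.01 is 1.53 and the formula gives 0.113.

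**How much comes from having several tests.** At ICC 0.01, counting any significant result among chi-square, logistic Wald, school-level t-test and an uncorrected robust standard error gives 0.133, against about 0.12 for the unadjusted tests alone. Most of the inflation comes from ignoring clustering.

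**How often the screen drops the arm when 29% v 19% is true.** This is one minus the simulated rejection rate:

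- ICC 0.01: 1 − 0.9365 = 6% unadjusted; 1 − 0.8231 = 18% at school level.
- ICC 0.094: 1 − 0.7877 = 21% unadjusted; 1 − 0.2996 = 70% at school level.

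These figures count the first screen only; the second round can only add removals.

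**The case against.** The best defence is that the screened regression is not the trial's arm comparison. Its stated purpose is to find independent factors influencing pregnancy, which matches the article's separate interest in associated factors, and intention-to-treat by assignment has its own sentence. The clustering sentence may be a general rule covering every test. School-level summaries, close to the remedy proposed here, are already planned. A condensed article may also leave detail to an analysis plan that is not shown.

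Much of this stands, and it rules out several stronger readings that a reader might infer:

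- *That the pregnancy conclusion rests on ordinary logistic regression.* Nothing makes that model decisive; cluster-aware methods and structural equation modelling are planned too.
- *That the t-tests test pregnancy as if girls were independent.* They are limited to continuous variables, and baseline comparison is one of their stated uses.
- *That a false positive is likely.* The inflation applies only if tests are run unadjusted, and at ICC 0.01 it is about 0.12.
- *That listing four estimators causes the inflation.* The figures above show that it adds little.
- *That availability, accessibility and perceptions replace the arm and so breach intention-to-treat.* Perceptions are recorded on clinic days, after allocation, but nothing says they stand in for assignment.
- *That the lack of a stated small-sample correction for robust or GEE tests is an error.* An analysis plan may supply it.

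What the defence does not remove: the logistic paragraph is assigned to the dependent–independent association, the service package is the named independent variable, and the arm is not exempted. Main analysis at both levels is stated, not merely left open. An analysis plan would have to override this text, not just complete it.

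**Conclusion.** The point holds in a limited form. No analysis is decisive for pregnancy, the written screen can remove or selectively report the randomised comparison, and the logistic and chi-square text is unreconciled with the clustering sentence.

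The arm-loss figures apply if the screen is used on the arm. The type I error figures apply if the tests are run on girls unadjusted; the article does not show that they will be. Both sets assume equal school sizes, 60 analysed per school unless stated, beta-binomial outcomes and no stratification. The range 0.011 to 0.094 is the article's own; its chosen 0.01 lies just below it, so both are shown. This should be settled before outcome data are seen by arm.

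**What to change.** Rewrite the analysis section so that:

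1. One analysis is primary for pregnancy: 12-month school-level proportions compared between randomised arms (9 v 9, t-test with 9 + 9 − 2 = 16 df), or alternatively one named cluster-adjusted individual-level model.
2. The arm is always in the model, and covariates are fixed in advance from the baseline factors in section 2.1.3.
3. P-value screening plays no part in the arm comparison.
4. Any chi-square, t-test or logistic comparison of arms is stated to be cluster-adjusted.
5. The other estimators are labelled sensitivity analyses. The risk-factor, availability/accessibility/perception and structural equation analyses are labelled exploratory.

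**Cost.** Wording only; no extra data. Intervals are wider than from a naive analysis by about √DE: 1.26 times at ICC 0.01, √3.95 = 1.99 times at 0.05 and √6.546 = 2.56 times at 0.094. Simulated power of the school-level t-test for 29% v 19% is 0.82 at ICC 0.01, but 0.45 at 0.05 and 0.30 at 0.094. That loss reflects the information in 18 schools; an unadjusted test would hide it, not recover it.

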**Rationale:** This study is particularly important because it seeks to identify feasible and tested measures to promote safe sexual behavior intended to prevent adolescent pregnancy across the world. Uganda in particular has persistently had an unacceptably high adolescent pregnancy prevalence of 25% for the last 10 years compared to 16% globally [4]. This means that one in every four (25%) adolescent girls between 15 and 19 years in Uganda is pregnant or has had their first child. Despite the numerous studies that have been conducted worldwide and in Uganda on the use of school-based sexual and reproductive health services, school-based sexual and reproductive health programs are widely accepted as an approach to reducing high-risk sexual behavior among adolescents; however, these face numerous challenges in the implementation and scale-up because of the exposure of contraceptives to the school-going adolescents. In addition, incentive-based interventions that focus on keeping young people in secondary school generally reduce adolescent pregnancy; thus, there is a continued need to provide health services to adolescents using various approaches. Schools may be a good place in which to provide these services [29]. Therefore, this study focused in particular on the provision of comprehensive SRH package to adolescents in school for the reduction in risky behavior and prevention of pregnancy.

There is very limited evidence focusing on the provision of multiple interventions used in the prevention of adolescent pregnancy in both developing and developed countries. Therefore, this study therefore seeks to implement multiple interventions through a School-Based Sexual and Reproductive Health (SBSRH) model which will include both SRH information and services in selected secondary schools and will investigate the effects of providing SBSRH services on prevention of pregnancy among adolescent girls in school aged 15–19 years in the Hoima District, Uganda.

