### 2.4. Sample Size

#### 2.4.1. Sample Size Calculation

The sample size will be calculated using the formula for comparing differences in rates and or proportions between two groups and determining the number of subjects per group *^n^*_Individual_Binary_ for a two-sided significance level *α* and power 1 − *β* [31]:$${}^{n}{}_{\mathrm{Individual}\_\mathrm{Binary}}=\frac{\left({}^{z}{}_{1-\alpha /2}+{}^{z}{}_{1-\beta }(2[{}^{\pi }{}_{T}(1-{}^{\pi }{}_{T})+{}^{\pi }{}_{C}(1-{}^{\pi }{}_{T})\right]}{{\left({}^{\pi }{}_{T}-{}^{\pi }{}_{C}\right)}^{2}}$$

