Structural equation modeling (SEM) using Analysis of a Moment Structures (AMOS) and Statistical Package for Social Sciences (SPSS) will be used to determine the statistical significance of the SBSRH model in the prevention of adolescent pregnancy. The constructs of the SBSRH model will be specified based on the theories that informed the research and the findings. Data of the identified constructs will be entered into the SEM software package. The package will fit the data to the SBSRH model and produces the results, which will include the overall model fit statistics and parameter estimates. Matrices of correlations and means will be used and relationships will be expressed as restrictions on the total set of possible relationships. The results feature overall indexes of model fit as well as parameter estimates, standard errors, and test statistics for each free parameter in the model.

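### The structural equation model is given a significance claim on pregnancy prevention, although it is described without randomised arm or school and partly specified from the findings

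*Protocol article*

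**What the plan says.** The SEM paragraph closes section 3 (Analysis) of the protocol article. It states the purpose of the SEM, to be run in AMOS and SPSS: it "will be used to determine the statistical significance of the SBSRH model in the prevention of adolescent pregnancy". On specification it says: "The constructs of the SBSRH model will be specified based on the theories that informed the research and the findings". On the input it says: "Matrices of correlations and means will be used and relationships will be expressed as restrictions on the total set of possible relationships". The outputs are overall fit indices and parameter estimates with standard errors and test statistics. The paragraph does not mention allocated arm, school, the unit of the data, the handling of a binary outcome, or an exploratory or secondary status.

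Earlier in the same section the article lists cluster-level, robust-standard-error, random-effects and GEE analyses, and says: "The intent to treat analysis will be used to analyze patients according to their random treatment assignment". Under the individual-level heading it adds: "Statistical tests will be conducted taking into account for the clustering effect".

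The Introduction (Rationale) uses the term for the programme itself. The study will "implement multiple interventions through a School-Based Sexual and Reproductive Health (SBSRH) model which will include both SRH information and services". The Introduction also commits to an a priori approach, in which the intervention is derived from existing theory and the proposed model is then implemented and tested. It names two theories, the Health Belief Model and the Trans-theoretical Model.

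**The concern.** The sentence on purpose attaches a statement of statistical significance about pregnancy prevention to an analysis that, as described, is not the randomised comparison. Paths between measured constructs and pregnancy are associations. The independent variable in section 2.1.1 is made up of availability, accessibility and perceptions of services, not the assigned arm. Data on perceptions of the service and provider are gathered on clinic days (Follow-up, section 2.8.3), that is, after randomisation. An intention-to-treat commitment elsewhere does not turn such paths into effects of allocation.

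Specifying constructs partly from the findings also fits badly with the a priori approach. If those findings are quantitative, the same data may both suggest and test the model. If they are qualitative, they are collected once during the 12 months of the study, so the constructs are still not fixed at the start.

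The results are meant to inform policy. A report could therefore cite the SEM as evidence of effectiveness alongside, or in place of, a randomised comparison that is less favourable.

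**Working it through.** **1. The passages side by side.**

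- Introduction: the SBSRH model is what is delivered to schools, and the proposed model is to be implemented and tested.
- Section 3, SEM paragraph: the SBSRH model has constructs, is fitted by software, and has its significance in preventing pregnancy determined.

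One term carries two meanings. Under the first, the SEM result is an efficacy claim. Under the second, it is a test of a conceptual model. The text does not separate them.

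**2. Inputs for the arithmetic.** The SEM paragraph contains no figure, so the plan's own clustering inputs are used: rates 0.29 and 0.19, ICC 0.01 and a cited range up to 0.094, cluster size m = 60 (all section 2.4.2), nine schools per arm (section 2.5), and alpha 0.05 "for a two-sided significance level" (section 2.4.1), so z = 1.96.

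**3. Reproducing the plan's figures.** Individual sample size per group: (1.96 + 0.842)² × [0.29 × 0.71 + 0.19 × 0.81] / 0.10² = 7.851 × 0.3598 / 0.01 = 282.5. Design effect: 1 + 59 × 0.01 = 1.59. Product: 282.5 × 1.59 = 449 per group, 898 in total. These agree with section 2.4.2.

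**4. If the SEM tested an arm contrast on individual girls without cluster adjustment.** Real type I error = 2 × [1 − Φ(1.96/√DE)], with DE = 1 + 59 × ICC.

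| ICC | DE | Type I error |
|---|---|---|
| 0.01 (plan) | 1.59 | 12.0% |
| 0.011 (lower end of cited range) | 1.65 | 12.7% |
| 0.05 (assumed, intermediate) | 3.95 | 32.4% |
| 0.094 (upper end of cited range) | 6.55 | 44.4% |

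A beta-binomial simulation (40,000 null trials per setting, 9 versus 9 schools of 60, null rates 0.29 and 0.19) gave 11.8% to 12.1% at ICC 0.01 and 44.4% to 45.0% at 0.094. A school-level t-test on the same data stayed between 4.8% and 5.2%.

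**5. If the paths join constructs that vary within schools.** The inflation is then roughly DE = 1 + 59 × ICC(construct) × ICC(outcome). The construct ICCs below are assumptions, since the article gives none.

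- Both ICCs 0.094: DE = 1 + 59 × 0.094 × 0.094 = 1.52, type I error about 11%.
- Outcome 0.01, construct 0.094: DE = 1 + 59 × 0.01 × 0.094 = 1.055, type I error about 5.6%.

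**6. What cannot be computed.** Any extra error from choosing constructs on the same data cannot be derived from the article.

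**The case against.** In its own paragraph the SBSRH model is something with constructs that software fits and that yields fit indices. That reads naturally as the testing of a conceptual framework, in keeping with the stated aim of developing one. The randomised analysis is set out first, is described as the key analysis at cluster and individual levels, and carries the intention-to-treat commitment. Nothing says that the SEM may override it. The findings may well be the interview and focus-group results, because the SEM paragraph follows directly after the thematic analysis. The article also has a general sentence on clustering, and estimator details are commonly left to a fuller document.

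Much of this stands. A reader might infer that the plan sets up a formal second efficacy test on 1080 girls treated as independent, with pregnancy treated as continuous and the model both built and tested on the same outcome data. The article states none of these things. Girl-level data are likely, since 18 schools could hardly support an SEM at school level, but that is an inference. So is a continuous outcome, and which findings are meant is open.

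The objection does not remove the sentence on purpose. It speaks of significance in preventing pregnancy, it uses the name that the Introduction gives to the programme, and no wording confines it to a supporting role. Calling other analyses key does not do so, particularly as none of the four listed approaches is marked primary. The clustering sentence sits under the individual-level analysis, and nothing in the SEM paragraph puts it into effect.

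**Conclusion.** The point holds as a defect in the SEM's assigned role and specification. As written, the plan allows a claim of statistical significance for the programme to rest on associations among constructs chosen partly from the findings, outside the randomised comparison. It does not show that such a claim will be made, nor that the SEM is the deciding test.

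The size is conditional. The figures of 12% at ICC 0.01 and 44% at 0.094 apply only to an arm contrast on individual girls without cluster adjustment, which the article does not state. They should not be read as the trial's false-positive rate, because the paths as described run among constructs and not from allocation. For constructs that vary within schools, the assumed ICCs above give about 5.6% to 11%. The case for change rests mainly on the non-randomised nature of the claim, which no cluster adjustment would cure.

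**What to change.** Reword the SEM paragraph in section 3 as follows.

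- Effectiveness is judged only on the cluster-adjusted intention-to-treat comparison of randomised schools.
- The SEM is exploratory, and no significance claim about the programme's effect is drawn from it.
- Its constructs are fixed from the two named theories, and from the qualitative findings if these are to be used, before outcome data are examined.
- The data level is stated, pregnancy is handled as binary, and standard errors respect schools, for example by resampling whole schools.
- Different terms are used for the delivered programme and the fitted structural model.

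The cost is a change of wording, some added analysis work (a school-level bootstrap or software that handles clustered binary outcomes), and a less prominent SEM result. No further data are needed.
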